| **Study Design** | This is a prospective, single-center, single-arm, phase II clinical study. This study plans to enroll 30 treatment-naïve and operable patients with locally advanced adenocarcinoma gastric. After signing the informed consent form, patients will be screened to ensure they meet the inclusion and exclusion criteria. Before surgery, patients will receive three cycles of neoadjuvant therapy with Serplulimab combined with the SOX regimen and nine weeks of thymalfasin. The efficacy of neoadjuvant therapy and the feasibility of radical D2 resection will be assessed via imaging after Cycle 2 and Cycle 3. Radical gastrectomy will be performed within 2–6 weeks after completing the third dose. The postoperative treatment of patients will be jointly decided by clinical physicians and patients according to the actual conditions of clinical diagnosis and treatment.  The main observation indicator is the pCR rate after neoadjuvant therapy;  Safety assessment: The safety will be assessed once after each cycle of neoadjuvant therapy and at 30 days after surgery;  Event follow-up: The events will be followed up every 3 months during the first year after surgery, and once every 6 months from the first to the second years, until the second year. |

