| Tumor tissue sample**^17^** | **X** | |  |  | **X** |  |  |
| **Notes:**   1. The screening period has a window of 28 days, the treatment period has a window of ±3 days (with a tumor assessment window of ±7 days), the end-of-treatment visit has a window of ±7 days, and the follow-up period has a window of ±7 days. During the screening period, ECOG performance status, hematology, blood biochemistry, coagulation, urinalysis, T3 or FT3, FT4, and TSH must be recorded within 7 days prior to the first dose and meet the corresponding inclusion and exclusion criteria for enrollment. 2. All prior treatments within 30 days before signing the ICF and all concomitant treatments from the signing of the ICF until the discontinuation of study treatment will be documented; thereafter, concomitant treatments for SAEs related to the study drug need to be documented. 3. Height examination is only performed in the screening period; vital signs include body temperature, pulse, respiratory rate and blood pressure. Body weight will be measured prior to each dose. If the subject's weight during the study changes by ≤10% compared to the baseline reference weight, no dose adjustment of the study drug is required. If the weight change exceeds 10%, the dose needs to be recalculated. 4. AEs and SAEs should be recorded from the signing of the ICF until 30 days after the last dose of the study drug. 5. Gastroscopy and pathology tests: Subjects must complete gastroscopy and pathology tests during the screening period after meeting the enrollment criteria and signing the informed consent form to determine the distance between the tumor and the incisors and collect tumor tissue specimens for subsequent laboratory tests. If gastroscopy and pathology tests have been performed at an external institution, gastroscopy must be repeated at this study site, but there are no requirements for pathology tests. 6. PD-L1 expression of gastric cancer: Subjects must complete the immunohistochemical PD-L1 expression and CPS scoring of gastric cancer tissues during the screening period after meeting the inclusion criteria and signing the informed consent form. They need to be completed at this study site. 7. MSI status of gastric cancer: Subjects must complete the immunohistochemical MSI status testing of gastric cancer tissues during the screening period after meeting the inclusion criteria and signing the informed consent form. They need to be completed at this study site. 8. Serplulimab will be administered on Day 1 of each 3-week treatment cycle after completion of all clinical and laboratory procedures/assessments. During the neoadjuvant phase, treatment consists of 3 cycles with a dose volume of 300 mg/dose. The dosing window is within ±3 days of the scheduled time point. 9. After completion of all clinical and laboratory procedures/evaluations, neoadjuvant therapy will be administered using the standard SOX regimen (oxaliplatin + Tegafur), with 3 weeks as one treatment cycle, and neoadjuvant therapy consists of a total of 3 cycles. Oxaliplatin will be administered on Day 1 of each cycle at a dose of 130 mg/m^2^, via intravenous infusion over 2–6 hours (chemotherapy drugs will be administered after the completion of Serplulimab infusion). If the body surface area exceeds 2.0 m^2^, the dose is calculated based on 2.0 m^2^. Tegafur will be administered orally according to the body surface area as below: <1.25 m^2^, 40 mg/dose; ≥1.25 to <1.5 m^2^, 50 mg/dose; ≥1.5 m^2^, 60 mg/dose; twice daily, from Day 1 to Day 14 of each treatment cycle. 10. After completion of all clinical and laboratory procedures/assessments, thymalfasin 4.8 mg will be administered via subcutaneous injection, twice weekly starting from Day 1 of neoadjuvant therapy. On Day 1 and Day 4 of each week during Weeks 1–9. 11. Routine laboratory tests include hematology, blood biochemistry, urinalysis, and coagulation function. The hematology items include complete blood count with differential. The blood biochemistry items include blood urea/urea nitrogen, creatinine, sodium, potassium, magnesium, chloride, bicarbonate/carbon dioxide combining power/total carbon dioxide (TCO2), calcium, phosphorus, glucose, total bilirubin, direct bilirubin, alanine aminotransferase (ALT), aspartate aminotransferase (AST), alkaline phosphatase, lactate dehydrogenase, total cholesterol, total protein, and albumin. The urinalysis items include specific gravity, pH, glucose, protein, casts, ketones, and blood cells. Coagulation function tests include activated partial thromboplastin time (APTT), prothrombin time (PT), and international normalized ratio (INR). The tests should be performed within 7 days before the first dose, within 3 days before dosing in Cycle 3, within 7 days before surgery, and within 3–7 days after surgery. If the laboratory tests and study drug administration are scheduled on the same day, the study drug cannot be administered until the test results are obtained. The analysis will be conducted in this study site. 12. Thyroid function tests include analysis of triiodothyronine (T3 or FT3), thyroxine (T4 or FT4), and thyroid-stimulating hormone (TSH). The tests should be performed 7 days before the first dose, 3 days before dosing in Cycle 3, 7 days before surgery, and within 3–7 days after surgery. The analysis will be conducted in this study site. 13. Cardiac function markers include: myocardial enzymes [creatine kinase (CK) and its isoenzymes], troponin (TnT or TnI), and brain natriuretic peptide (BNP and/or NT-proBNP). The tests should be performed 7 days before the first dose, 3 days before dosing in Cycle 3, 7 days before surgery, and within 3–7 days after surgery. The analysis will be conducted in this study site. 14. Tumor markers must include: carcinoembryonic antigen (CEA), carbohydrate antigen CA19-9, and alpha-fetoprotein (AFP). The tests should be performed 7 days before the first dose, 3 days before dosing in Cycle 3, 7 days before surgery, and within 3–7 days after surgery. The analysis will be conducted in this study site. 15. Pre-transfusion eight-item panel: All subjects must undergo hepatitis B surface antigen (HBsAg) and hepatitis B core antibody (HBcAb) testing during the screening period. For subjects with HBsAg (+) or HBcAb (+), further hepatitis B virus (HBV) DNA titer testing is required. At screening (baseline), in case of HBV DNA (-), and either 1. HBsAg (+), or 2. HBcAb (+), HBsAg (-), then HBV surface antigen/core antibody and HBV DNA must be tested every 2 cycles during treatment, before the surgery, at treatment discontinuation, and during safety follow-up. 16. CT or MRI imaging examinations should be performed within the screening period, within 7 days before treatment in Cycle 3 of neoadjuvant therapy, within 1 week after completion of neoadjuvant therapy, and after the surgery until the initiation of adjuvant therapy (recommended 4–12 weeks after the surgery). Throughout the study period, the examination methods should remain as consistent as possible. Abdominal CT scans require dual-phase (arterial and venous) imaging, performed under fasting conditions with the intake of at least 1000 mL of water or contrast agent. Contrast agents should be used unless contraindicated. The investigator assesses tumor imaging findings according to RECIST v1.1 (the frequency of tumor assessments may be increased as clinically needed at the investigator's discretion). The investigator should determine subsequent treatment based on the efficacy evaluation results. If tumor assessment has been performed within 28 days prior to the first dose, and the same method and equipment are used at the same hospital, it may serve as the baseline tumor assessment. 17. Subjects must provide formalin-fixed, paraffin-embedded (FFPE) tumor samples (paraffin blocks or unstained sections) collected from the lesion site at or after GC diagnosis (preferably within 2 months before the first dose of the study drug), along with relevant pathological reports of the aforementioned specimens. If the subject does not have archived tumor tissue samples that meet the requirements, a fresh tumor lesion biopsy must be performed during the screening period to obtain corresponding tumor samples (the number of specimens collected will be determined based on the biopsy). Additionally, surgically excised tumor tissue specimens will be retained postoperatively. Tumor tissue section samples will be used for determination of PD-L1 expression levels and MSI testing. | | | | | | | |

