- Safety of neoadjuvant immunization + chemotherapy + thymalfasin: Observe any adverse events occurred in all patients during the clinical study, including abnormalities in laboratory tests of abnormal clinical symptoms and vital signs, record their clinical manifestations, severity, occurrence time, duration, treatment methods and prognosis, and determine their correlation with the test drug. Drug safety will be evaluated by NCI-CTCAE version 5.0 criteria. Meanwhile, the incidence of Grade 3–4 adverse events will be recorded from the start of neoadjuvant therapy to 30 days after surgery; the proportion of neoadjuvant therapy-related AEs causing surgical delay more than 30 days or inoperable beyond the original plan;
  - 1. **Exploratory endpoints**

Biopsy tissue specimens before neoadjuvant therapy and paraffin-embedded pathological tissue specimens after surgery will be collected from cases meeting the inclusion and exclusion criteria, and the expressions of CD68, CD86, CD163, CD4+T cells, and CD8+T cells will be detected.

1. **Study Design**

This is a prospective, open-label, single-arm phase II clinical study to assess the efficacy and safety of Serplulimab in combination with thymalfasin and SOX regimen for neoadjuvant therapy of locally advanced gastric cancer. It is planned to enroll 30 patients with HER2-negative gastric or gastroesophageal junction adenocarcinoma confirmed by histopathology and/or cytology who were clinically staged as stage III resectable G/GEJ carcinoma (Siewert type III and Siewert type II not requiring combined thoracotomy) as assessed by endoscopic ultrasonography, CT/MRI and other imaging. Endoscopically, gastric tumor tissues will be collected from patients for immunofluorescence detection while clamping gastric tumors for pathological examination.

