**Body surface area (m^2^), first dose (as Tegafur):**

<1.25 m^2^, 40 mg/dose

≥1.25 m^2^ to <1.5 m^2^, 50 mg/dose

≥1.5 m^2^, 60 mg/dose

- 1. **Postoperative Follow-up Period**

1. The occurrence of postoperative complications should be followed up within 30 days after surgery;
2. All enrolled subjects will be continuously monitored: patients who receive surgery will be followed up every 3 months within the first year after surgery and every 6 months thereafter until 2 years, with the following recorded: physical examination, laboratory test results (including tumor marker tests), imaging findings (presence of recurrence or metastasis), adjuvant treatment regimens, and treatment duration.
3. **Use of Study Drugs**
   1. **Serplulimab**

Serplulimab from Shanghai Henlius Biotech, Inc. is used in this study, with a strength of 100 mg/vial. The main active ingredient of Serplulimab is a recombinant fully human anti-programmed death receptor-1 (PD-1) monoclonal antibody, with a concentration of 10 mg/mL. This product is a clear, colorless liquid, free from foreign matter, flocculent material or precipitate. The excipients include citric acid, sodium citrate, sodium chloride, mannitol, polysorbate 80, and water for injection.

The finished product of Serplulimab should be stored protected from light at 2–8℃, with a shelf life of 36 months. If turbidity, precipitation, or other quality issues are observed in the injection solution, the product should be immediately stored in sealed containers and Henlius should be notified immediately.

The intravenous infusion time of Serplulimab should be 30–60 minutes. Do not administer by intravenous bolus or a single rapid intravenous injection. Dilution instructions for the drug prior to administration are as follows:

- Prepare the solution and perform infusion
- Do not shake the vial.
- Allow the vial to return to room temperature (25°C or below) before use.
- After taking it out of the refrigerator, the vial may be stored at room temperature (25°C or below) for up to 24 hours prior to dilution.
- Visually inspect the solution for injection for particulate matter and discoloration prior to administration. This product is a clear to slightly opalescent, colorless to pale yellow liquid, free from foreign matter. If visible particles are observed, the vial should be discarded.

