All AEs, including SAEs, observed by the investigator or spontaneously reported by subjects from the signing of the informed consent form until 30 days post-surgery, will be collected.

- - 1. **Follow-up of adverse events**

AEs should be followed up until they return to baseline or Grade 0–1, or until the investigator deems further follow-up unnecessary for justified reasons (e.g., the AE cannot resolve or has improved). If the AE cannot resolve, a reasonable explanation must be documented in the CRF. Regardless of whether it is related to the study drug, the recovery status and date of the subject's AE or SAE should be recorded in the CRF and medical records.

- - 1. **Recording content of AEs**

The investigator must fully document any AE, including diagnosis (or symptoms, signs, and abnormal laboratory findings if no diagnosis is available), start and end dates and times (if applicable), CTCAE severity grade and changes (for Grade 3 or higher events), whether it is a SAE, measures taken regarding the study drug, treatments administered for the AE, outcome of the event, and the relationship between the AE and the study drug.

For any SAE, the investigator should also provide the date when the AE meets SAE criteria, the date when the investigator becomes aware of the SAE, the basis for classifying the AE as an SAE, dates of hospitalization and discharge, possible cause of death, date of death, whether an autopsy is performed, causality assessment with the study procedures, causality assessment with other medications, and other potential causes leading to the SAE.

The investigator should also provide the rationale for causality assessment and a description of the SAE. In the SAE description, the following must be included: subject No., age, sex, height, and weight; the indication for the study drug treatment, disease stage, and relevant systemic conditions; the clinical course of the SAE, including its onset, progression, outcome, and final result; laboratory test results related to the SAE (the test time, units, and normal reference ranges must be provided); medical history related to the SAE, comorbidities, and their onset and duration; medication history related to the SAE, concomitant medications, and details of their initiation, duration, and dosage and administration; as well as detailed information on the study drug treatment, including its initiation, duration, dosage and administration.

The description of AE records is as follows:

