**Death**

All deaths occurring during the entire study, including the 30-day follow-up period after the last dose, regardless of their relationship to the study drug, should be recorded in the Death Report Form of the CRF and promptly reported to the sponsor.

When recording death events, if the cause of death is clearly identified, the cause of death shall be documented as an AE, with the outcome of the AE being death, and the event shall be reported as a SAE (deaths due to tumor progression or deaths occurring 30 days after the last dose that are considered not related to the study drug, and are not recorded or reported as AEs/SAEs; however, the investigator shall document the death in the Death Report Form of the CRF and promptly notify the sponsor). If the cause of death is unknown at the time of reporting, it shall be recorded as "death of unknown cause" in the Adverse Event Form of the CRF, and "death of unknown cause" shall initially be reported as an SAE, followed by further investigation to determine the exact cause of death.

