**Reporting of SAEs:**

The reporting period for SAEs is from the signing of the informed consent to 30 days after surgery (inclusive). In the event of an SAE, whether it is an initial report or a follow-up report, the investigator must promptly complete the Serious Adverse Event Report Form, sign and date it, and report it to the sponsor within 24 hours of becoming aware of the event. Meanwhile, SAEs occurring after using Henlius products shall be reported to Henlius: ([contact]) within 24 hours after awareness, and the SAE occurring after using SciClone products shall be reported to SciClone ([contact]) within 24 hours after awareness.

If a SAE occurring outside the aforementioned period is determined to be related to the study drug, it should also be reported.

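### The flow chart ends AE and SAE recording 30 days after the last dose, while the safety endpoint and Section 11 run to 30 days after surgery

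*Protocol*

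**What the plan says.** The Protocol gives two different ends for recording adverse events.

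**Anchored to the last dose**
- Study Flow Chart, Note 4: "AEs and SAEs should be recorded from the signing of the ICF until 30 days after the last dose of the study drug". The AE row is marked from screening to the surgery and treatment-discontinuation columns, with no mark under follow-up. The first follow-up visit comes 3 months after surgery.
- Section 11.4, Death: all deaths go on the Death Report Form and to the sponsor. However, "deaths occurring 30 days after the last dose that are considered not related to the study drug" are not recorded or reported as AEs or SAEs.

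**Anchored to surgery**
- Section 2.2, safety endpoint: "the incidence of Grade 3–4 adverse events will be recorded from the start of neoadjuvant therapy to 30 days after surgery".
- Section 11.4, collection and time frame: AEs and SAEs "from the signing of the informed consent form until 30 days post-surgery, will be collected".
- Section 11.5: "The reporting period for SAEs is from the signing of the informed consent to 30 days after surgery (inclusive").
- Synopsis, Study Design: "The safety will be assessed once after each cycle of neoadjuvant therapy and at 30 days after surgery".
- Section 6.3: "The occurrence of postoperative complications should be followed up within 30 days after surgery".

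**The concern.** The two windows differ by the whole interval between the last dose and the operation, which the design sets at 2–6 weeks. A flow chart is what study staff usually work from, and this one contains no 30-day postoperative prompt to offset Note 4.

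Safety is part of the primary objective, and perioperative complications are named in a secondary endpoint. Events missed after surgery would lower the reported incidence. With 30 patients planned, each patient whose only qualifying event is missed moves an incidence by 1/30 = 3.3 percentage points.

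Two related gaps follow. The Death paragraph and Section 11.5 can classify the same postoperative death differently. And a window that ends 30 days after surgery has no end for a patient who has no surgery, although Section 5.1 foresees patients who become ineligible for resection.

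**Working it through.** The plan states no figure to reproduce, so the check is day arithmetic.

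**Inputs**
- Day 1 is the first dose and cycles last 21 days, so the third infusion is Day 1 + 2 × 21 = Day 43.
- Tegafur runs Days 1–14 of each cycle, so its last day is 43 + 13 = Day 56.
- Thymalfasin is given on Days 1 and 4 of Weeks 1–9, so its last dose is 8 × 7 + 4 = Day 60. The synopsis adds an alternative of continuing until surgery, which the flow-chart notes, Section 3 and Section 6.2 do not.
- Surgery is 14–42 days after the third dose (synopsis, Section 3), or in Weeks 2–6 after the last chemotherapy plus immunotherapy (Section 6.2). The second wording could be counted from the end of tegafur.

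**Formula.** Postoperative days covered = max(0, min(30, last dose + 30 − surgery day)). Days lost = 30 − days covered.

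Example, with the last dose and the surgery interval both counted from the third infusion: Note 4 closes on Day 43 + 30 = Day 73. Surgery at week 2 is Day 57, so 73 − 57 = 16 days are covered and 14 lost. Surgery at week 6 is Day 85, so Note 4 closes 12 days before the operation and all 30 are lost.

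Postoperative days lost, by week of surgery:

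| Last dose taken as | Surgery counted from | Wk 2 | Wk 3 | Wk 4 | Wk 5 | Wk 6 |
|---|---|---|---|---|---|---|
| Third infusion, Day 43 | Third infusion | 14 | 21 | 28 | 30 | 30 |
| End of tegafur, Day 56 | End of tegafur | 14 | 21 | 28 | 30 | 30 |
| Thymalfasin, Day 60 | Third infusion | 0* | 4 | 11 | 18 | 25 |
| Thymalfasin, Day 60 | End of tegafur | 10 | 17 | 24 | 30 | 30 |

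*This cell puts surgery on Day 57 and a thymalfasin dose on Day 60, after the operation. If the last dose is instead Week 8 Day 4 (7 × 7 + 4 = Day 53), the window closes on Day 83, 83 − 57 = 26 days are covered and 4 are lost.

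If thymalfasin continues until surgery, twice-weekly dosing puts the last dose at most 4 days before the operation, so about 0–4 days are lost.

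**Deaths.** Take surgery at week 4 (Day 71) and a fatal surgical complication 20 days later (Day 91), judged unrelated to study drug. That is 48 days after the third infusion and 31 days after thymalfasin on Day 60. Reading the Death paragraph's phrase as later than 30 days after the last dose, this death is exempt from AE/SAE recording. It falls 20 days after surgery, so Section 11.5 requires it as an SAE.

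**Unoperated patients.** Sections 11.4 and 11.5 date the end of the window only from surgery. Note 4 is the only general AE end date that such a patient could meet.

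**Grades (separate and minor).** The Section 2.2 incidence counts Grades 3–4. The grading table in Section 11.3 defines Grade 5 as death related to an AE, so a fatal event is outside that count as worded.

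**The case against.** The strongest reply is that Note 4 is the outlier and other rules catch most of what it would drop. The synopsis plans a safety assessment 30 days after surgery, and Section 6.3 follows complications for the same period. The synopsis grades surgical safety on its own scale, and Section 11.5 keeps drug-related SAEs reportable outside the window. The chart marks AEs at the surgery visit, which tells against stopping before the operation. All of this stands, and it limits the loss. It does not replace AE and SAE recording for the Section 2.2 endpoint, which is not restricted to drug-related events or surgical complications, or the reporting of SAEs judged unrelated.

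A reader might infer more than the text supports on four points:
- **That postoperative deaths go unrecorded.** They do not. The Death paragraph sends even the exempt deaths to the Death Report Form and the sponsor. Only their AE/SAE classification is in conflict.
- **That most postoperative safety data will be lost.** This holds only if staff follow Note 4 over Section 11, and only on some readings of the last dose. The synopsis describes one center, so the issue is not divergence between sites.
- **That the measure of surgery delayed by AEs is undermined.** Events that delay surgery occur before it, and the arithmetic here concerns the days after.
- **That Grades 3–4 in Section 2.2 contradicts the synopsis.** The synopsis item of Grade 3 or higher concerns treatment-related events, which is a different quantity.

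**Conclusion.** The contradiction is in the current text and holds. Following Note 4 costs 14 to 30 of the 30 postoperative days if the last dose is the third infusion. With thymalfasin on Day 60 it costs up to 25 days if surgery is counted from the third infusion, and 10–30 if counted from the end of tegafur. It costs about 0–4 days if thymalfasin continues until surgery. The spread arises because the last dose of study drug is undefined: the synopsis lists Serplulimab and thymalfasin as study drugs, while Section 7 covers all four agents.

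The figures assume dosing on schedule, surgery inside the 2–6 week window, and staff who take Note 4 literally. The Death paragraph's conflict with Section 11.5 and the missing end date for unoperated patients also stand.

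This is an internal inconsistency that should be fixed. It affects a secondary safety endpoint and SAE reporting; the pCR endpoint is untouched.

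**What to change.** 1. Reword Note 4 so that recording runs from consent to 30 days after surgery, as Sections 2.2, 11.4 and 11.5 already state, and add a 30-day postoperative mark to the flow chart's AE row.
2. Reword the Death paragraph so that its AE/SAE exemption for unrelated deaths does not apply within 30 days after surgery. Keep the Death Report Form rule as it is.
3. For patients who are never operated, state an end date based on the last dose of any study drug.
4. Define the last dose by naming the drugs that count. Reconcile the synopsis with the other sections on when thymalfasin ends, and state which dose the surgery interval is counted from.
5. Separately, let the Section 2.2 incidence count Grade 3 or higher, so that fatal AEs are included.

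The cost is wording, one added mark in the chart, and AE recording at the 30-day postoperative assessment that the synopsis already plans.
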